## Abstract

**Background:**

This study protocol describes a proposed randomized controlled trial that builds upon a successful pilot intervention study to address problematic and dangerous drinking among young adult college students studying abroad in foreign environments. Despite universities and colleges citing alcohol misuse as the most concerning issue for their students abroad, most institutions offer no empirically-based prevention efforts tailored to this at-risk population. The proposed intervention attempts to fill a major gap for the nearly 333,000 students completing study abroad programs each year by using empirically-based and theoretically-informed risk and protective factors to correct misperceived peer drinking norms and promote cultural engagement abroad. In addition to preventing heavy and problematic drinking, the intervention seeks to prevent risky sexual behaviors (e.g., sex without a condom) and experience of sexual violence victimization, which are strikingly common among study abroad students and have the potential for lasting physical and psychological effects upon return home.

**Methods/design:**

We will conduct a randomized controlled trial of an intervention with a sample of 1200 college students studying abroad from approximately 50 US universities and colleges. The brief, online intervention is text and video based and contains evidence-based components of personalized normative feedback to correct students’ misperceived drinking norms, content to promote engagement with the cultural experience abroad and address difficulties adjusting to life in the foreign environment, and tips and strategies to prevent risky sexual behaviors and sexual violence victimization abroad. Participants will complete online surveys at five time points (predeparture, first month abroad, last month abroad, 1-month post-return, and 3-months post-return) to assess for intervention effects on drinking behavior, drinking consequences, risky sex, and sexual violence outcomes. We will examine whether the mechanisms targeted by the intervention (changes in perceived norms, engagement in the cultural experience abroad) serve as mediators of intervention efficacy.

**Discussion:**

The proposed study has the potential to fill an important gap in the research literature and provide empirical support for an online accessible, brief, and targeted approach that can easily be distributed to study abroad students to help prevent heavy alcohol use and sexual risk abroad.

*Trial registration* ClinicalTrials.gov Identifier NCT03928067

## Background

The number of young adult students taking advantage of opportunities to study abroad during college is growing. Approximately 1 in 10 American undergraduate college students study abroad before graduating, with nearly 333,000 students completing study abroad experiences in the 2016/2017 academic year [1]. This represents a 120% increase over the past 15 years. The personal, cultural, and academic benefits of study abroad are many and include increased global perspectives, enhanced self-esteem, preparation for international careers, respect for other cultures, and academic success [2–8].

### Study abroad students are at-risk for heavy drinking and negative sexual consequences

Despite these benefits, American study abroad students represent a large and diverse population at-risk for increased and problematic drinking. Students more than double their weekly alcohol use while abroad and both pre-abroad inexperienced drinkers and the heaviest drinkers abroad return home drinking at higher levels than before they left [9–11]. A substantial portion of students face negative alcohol-related consequences while abroad [9, 10]. For example, in one study, more than one-third of study abroad students reported taking risks or doing impulsive things while drinking they later regretted [9], and in another study, at least 1 in 10 students reported drinking to the point of passing out or blacking out, missing classes, finding themselves in dangerous situations, or experiencing alcohol-related injuries [10]. The novelty of the abroad context creates a wider range of abroad-specific consequences than are present on campus (e.g., offending host families, losing passports, disrupted travel plans) [9]. In addition, consequences may be exacerbated abroad or develop into long-term problems due to limited access to resources and familiar coping strategies (e.g., being far from friends/family; being unfamiliar with local healthcare locations or law enforcement policies). University administrators and personnel working with study abroad students also report substantial concerns with their students’ drinking behavior abroad [12–15].

In addition to heavy drinking, students are also exposed to a number of sexual risks while abroad, including risky sexual behaviors (e.g., unprotected sex with multiple partners) and sexual violence (ranging from non-consensual sexual contact to attempted and completed sexual assault by force) [16]; many of these risks are amplified by heavy drinking. A well-established line of research with college students on campus indicates that heavy alcohol use increases risky sexual behavior, and is associated with increased risk for sexual assault victimization and perpetration among both male and female students [17–20]. Increases in heavy drinking within a novel environment alone may place students at risk for sexual violence victimization. Back on campus, at least half of sexual violence incidents on campus involve victim and/or perpetrator drinking; most often both are intoxicated [19, 21]. Heavy drinkers are most at-risk, but even light or non-drinkers that engage in heavy drinking during a particular situation (such as during an abroad trip) are at increased sexual risk [22]. Thus, the nature of heavy drinking abroad, coupled with unique risks found in the abroad environment, likely contribute to greater sexual risk abroad.

The literature on sexual risk abroad is only emerging, however, small cross sectional studies from single universities have shown that between 25 and 50% of male and female students report risky sexual behavior [9, 23, 24], upwards of 75% of female students report some form of sexual victimization while abroad [23–26], and female students are at three times higher risk for attempted sexual assault and five times higher risk for completed sexual assault abroad compared to their risk back home on campus [25], where rates are already high (upwards of 1 in 5 female students) [27]. Men are also not immune to sexual victimization abroad; in one study nearly 1 in 10 reported pressure to have sex with someone while intoxicated [9]. These events can ruin study abroad experiences and lead to lasting physical and psychological effects (e.g., sexually transmitted infections, pregnancy, trauma).

### The need for evidence-based prevention programs specific to study abroad risk

A review of study abroad drinking revealed that while there is ample evidence showing that drinking in study abroad contexts is more problematic than domestic on-campus drinking, there has been little attention or targeted interventions aimed at this high-risk environment [28]. In addition, content analysis of 753 US study abroad program websites revealed that institutions provide limited information about alcohol use and sexual risk on their websites [29]. Furthermore, although study abroad program directors report that they discuss alcohol and associated sexual risks with their students prior to abroad [30], the majority of students report that they do not receive any predeparture alcohol or sexual risk programming [31]. Thus, a program designed to target this large at-risk group and the unique risk factors faced abroad has the potential to fill an important gap and produce widespread and lasting physical and/or psychological benefits. Though most college campuses provide all students alcohol programs and sexual violence prevention programs, the nature and extent of heavy drinking, risky sex, and sexual victimization abroad are very different than on campus, and programs geared toward all students (and in particular, those on campus) may not target the specific risks experienced by students when the go abroad. Increased drinking rates combined with unfamiliar surroundings, impaired judgment around the prudence of certain behaviors in the novel cultural environment, and limited comprehension of the nuances of local culture may increase the potential for negative alcohol and sexual outcomes. Thus, there is a need for prevention programs specifically targeted toward study abroad students and their unique risks in the novel environment.

### Risk and protective factors for study abroad students

#### Normative drinking misperceptions

Incorrect perceptions of drinking abroad are a major factor contributing to increased and problematic drinking while studying abroad. Within the study abroad environment, perceived norms of study abroad peers are robustly associated with heavy drinking abroad and predict increases in drinking behavior from predeparture to during the abroad experience [9, 32, 33]. In addition to perceptions of other US student peer drinking while abroad, perceptions of the normative drinking of native young adults in one’s host country are uniquely associated with student drinking [32], such that if a student believes local people are heavier drinkers, he or she is, in turn, likely to drink more heavily as well. This is true even when controlling for per capita alcohol consumption in the students’ host countries [32], suggesting that perceptions of what local people are doing are more influential on personal drinking than the actual drinking levels of the host country.

Targeting misperceptions of peer alcohol use through personalized normative feedback (PNF) interventions can correct misperceptions and prevent heavy drinking during high-risk events. Correcting misperceptions of peer drinking norms through PNF has become one of the most prominent strategies for addressing excessive alcohol use among college students [34–38]. Interventions based solely on PNF have demonstrated small to large effect sizes [39–41], with changes in perceptions of peer behavior mediating intervention effects [42–45]. Even in interventions that include several components in addition to PNF, the effects are generally mediated by augmented normative perceptions rather than variables associated with the other components typical to brief interventions (e.g., weighing pros and cons of changing behavior) [46–48]. Most of this research has focused on reducing pre-existing drinking patterns; however, in recent work, PNF interventions have been adapted to proactively prevent drinking during specific future events known to represent heightened risk, such as 21st birthday and spring break trips [41, 49–51].

In our pilot work with a sample of 343 study abroad students from one university, we found that providing PNF focused on salient and proximal reference groups (i.e., study abroad peers; country-specific young adults native to one’s host country) prior to their departure helped students form more accurate beliefs about drinking within their host country and prevented escalation of drinking while abroad [52]. However, we also found that heavier drinking students that received PNF alone failed to report significantly less drinking during abroad than those heavy drinkers not receiving PNF. This may be because students expect to drink more while abroad and believe alcohol will be a central part of their abroad experience [9]. Helping students navigate this unique environment could reduce risk and consequences. In addition, a key aspect of PNF is that, after learning the actual norms for their environment, participants confirm the veracity of these new norms themselves by observing the behavior of peers and local people post intervention. However, this critical norm confirmation step is missed among students abroad who spend little time engaging their new cultural environment (e.g., spending most of one’s time socializing with other American students) because such students avoid the local sociocultural environment where these cross-cultural drinking norms would be visible. Thus, study abroad students may require an additional innovative approach that not only addresses the perceived norms that can contribute to increased drinking while abroad, but also addresses the importance of understanding one’s host country and the study abroad context. Doing so can help students navigate this new environment more successfully and therefore be less likely to drink heavily.

#### Sojourner adjustment

Poor adjustment into the foreign environment and limited engagement with the local culture represent additional risk factors for heavy drinking while abroad. Theories of acculturation [53, 54] and, more specifically, sojourner adjustment (i.e., the sociocultural and psychological adjustment of relatively short-term visitors to new cultures) [55] posit that immigrants and students who attempt to integrate or assimilate more fully into their new culture are at the least risk for sociocultural and psychological adjustment difficulties [53, 54, 56–60]. Research and theory also suggest that if young people transition to a temporary novel risky environment (e.g., spring break, Mardi Gras in New Orleans) and they do not feel connected to their environment, they may view their time as a temporary reprieve from real life (i.e., a “backspace”), transgress drinking and sexual norms, act in ways inconsistent with their personalities, and, thus, be more likely to engage in risky behaviors such as heavy drinking and risky sex [61–64].

Our research with American study abroad students suggests that those most at-risk for heavy drinking and consequences are those who separate themselves from the host environment (i.e., placing more emphasis on the home/US culture), those who perceive the abroad culture as very different than their home culture, those who spend more time with other Americans while abroad, those who feel out of place being away from home, and those who experience anxiety about interacting in the foreign environment [9, 32]. Other work has confirmed that this *negative* sojourner adjustment is associated with greater risk for heavy drinking and problems abroad [65, 66]. Conversely, we have also found that *positive* sojourner adjustment (i.e., quality/quantity of time with local people, active engagement with cultural experiences and events, foreign language development/use, identification as a member of the host culture) protects students from heavy alcohol use and problems [10]. Thus, promoting cultural engagement and helping with adjustment/transition to life in a foreign environment may prevent incidences of problematic drinking abroad [2, 67–69]. Positive sojourner adjustment can relate to taking advantage of cultural learning experiences by participating in local customs and spending time with local people, rather than focusing on drinking-centered social experiences with other American students. Culturally-engaging activities may also serve as healthy alternatives and provide a means of achieving social and recreational goals without drinking [70], potentially reducing motivation to drink for both social and coping reasons and, therefore, reducing alcohol use and consequences while abroad. Importantly, preventing heavy drinking patterns from forming abroad may also prevent continued heavy drinking once students return home.

#### Targeting both normative drinking misperceptions and sojourner adjustment

Our work has shown that study abroad students who greatly overestimated drinking behavior and who reported negative sojourner adjustment had the highest risk of drinking and consequences [32]. It was also evident from our pilot study that providing PNF alone, which works well for students back on campus, was not a sufficient stand-alone intervention for study abroad students—an established heavy drinking group at risk for multiple negative consequences. Misperceived norms back on campus are based on years of observation of peers (Social Learning Theory [71]; e.g., noticing the few heavy drinkers at a party and falsely believing these heavy drinkers are the majority) and the perpetuation of college heavy drinking stereotypes (e.g., movies such as *Animal House* and *Old School*; discussions with friends about the parties that occurred). Yet study abroad students are entering a new environment with little to no context to make predictions about what drinking norms may look like in the foreign country (both by their study abroad peers and by local young adults). The promotion of cultural engagement in addition to PNF can help students better understand ways to engage in this new environment without the exclusive company of their American peers, affording valuable opportunities to observe that their perceptions of drinking may have been inaccurate. Our pilot work showed that students provided with sojourner adjustment feedback (SAF) in addition to PNF prior to departure abroad experienced significantly fewer alcohol-related consequences abroad compared to students in a control condition, with the greatest benefits for the most at-risk students—those reporting heavier consequences at predeparture [52].

#### Other risk factors

Risk factors inherent to the abroad environment are also present and will likely impact any intervention effects on programming seeking to prevent heavy drinking and problems abroad. Many students may be going abroad before they turn 21 years old, which is the legal age to purchase and consume alcohol in the United States, but in nearly all countries that students travel to, the drinking age is lower. Thus, students may be studying abroad in cultures where it is now legal for them to access alcohol and research shows that those under 21 are at greater risk for increased drinking abroad [11, 72]. Moreover, where students choose to travel is associated with their drinking behaviors, with students studying in European countries and Australia drinking more heavily than students studying in other countries. Gender is also important as longitudinal studies show increases in drinking for both genders but greater drinking abroad for men [11, 72]. Furthermore, those with more socially motived reasons for drinking and those who may be drinking to cope (e.g., to alleviate feelings of homesickness or feeling out of place) tend to drink at greater levels abroad [10, 65], and those students who believe alcohol will play a large role in their study abroad experience report more alcohol-related consequences while abroad [9].

### The present study

Expanding on our promising pilot findings, we designed the present study to refine and further test the PNF + SAF intervention in five specific ways with a large sample of students across multiple diverse colleges and universities in the US. First, discussions with users of the pilot program indicated that the text-heavy feedback presented was too broad and difficult to absorb. Thus, we will update the normative content to reflect drinking in one’s specific country of study and make the SAF more interactive, including video testimonials from study abroad students discussing engaging in the culture and staying safe abroad. Second, given emerging research highlighting increased risk for study abroad alcohol-related risky sexual behavior and sexual victimization [24–26], we will include content on preventing sexual risk and evaluate sexual risk outcomes. Third, we will expand on the small pilot study to test the refined brief, online preventive approach with a proposed 1200 students on a large scale across multiple universities and colleges (i.e., 50+ institutions that have expressed interest in helping us with recruitment of their students). Fourth, we will examine effects on heavy drinking and consequences during both the high-risk event as well as when students return, as these students are at risk for increased drinking post-return compared to their non-study abroad peers [10, 66, 73]. Finally, we will test mediators of changes in perceived norms and reports of sojourner adjustment abroad (the mechanisms targeted in the intervention) and moderators of intervention efficacy known to be associated with problematic use abroad. Mainly, we will test whether younger students (i.e., those under age 21), men, those studying in Europe, those who drink for social and coping reasons abroad, those with expectancies that alcohol will play a large role in their experience while abroad, and baseline heavier drinkers will benefit most from the PNF + SAF intervention [9–11, 52, 65, 72]. We will also examine history of sexual violence prior to abroad as a moderator of intervention effects on sexual violence outcomes, given prior work documenting that sexual violence history moderates outcomes in online-delivered alcohol and sexual violence programming [74, 75].

## Methods/design

### Overview

The present study will occur in two phases. Phase 1 will involve a large-scale documentation of the drinking patterns of a proposed 2500 students studying abroad and the video collection of testimonials/advice from a proposed 20 students who have previously studied abroad. Normative drinking content and video footage from study abroad students will be used to develop the intervention. In Phase 2, we will conduct a parallel group randomized controlled trial (RCT), where we will test the enhanced intervention among a different sample of 1200 students from approximately 50 US institutions. We will test the efficacy of the intervention on preventing problematic drinking behavior, risky sexual behaviors, and experiences of sexual violence in this high-risk environment during the first and last month abroad and on sustained effects once students return to campus at 1- month and 3- months post-return. The hypotheses are that those student participants who receive the intervention will drink less, experience fewer alcohol-related consequences, engage in fewer risky sexual behaviors, and experience lower rates of sexual violence abroad and back home on campus compared to student participants in a control group.

### Participants

Students will be deemed eligible to participate if they (1) are between the ages of 18 and 24, (2) are signed up to study abroad in one of the 12 most popular destinations (i.e., United Kingdom, Italy, Spain, France, Germany, China, Ireland, Australia, Costa Rica, Japan, South Africa, and Mexico; representing 60% of study abroad students [1]), and (3) plan to study abroad for between 8 and 20 weeks (approximately one quarter/semester), which represents about two-thirds of all student abroad students [1].

### Procedures

Representatives from the study abroad offices at the 50 institutions will email prospective students to inform them about the study. Interested students will fill out an online sign-up sheet to assess eligibility. We will then randomly invite students into the study to ensure we have adequate numbers of both male and female genders represented. Invited students can consent to participate in the study and fill out measures collected online. Participants’ confidential data will be tracked by PIN codes. Participants will read an electronic IRB consent form and indicate consent before enrolling in the study. We will recruit 1200 participants who will be randomly assigned to the intervention condition (N = 600) or a control condition (N = 600). Intervention participants will receive the 30 to 40 min intervention as described below. Control participants will receive a link to a general website offering study abroad advice and will be asked to spend at least 30 to 40 min reviewing their institution’s study abroad website content, including policies for drinking abroad. This control condition was selected as a form of “treatment as usual” as our conversations with study abroad personnel indicated this is the extent of typical information students receive about alcohol use abroad. Many students also attend predeparture informational orientation sessions where alcohol use and sexual risk may or may not be briefly discussed; we will control for receipt of orientation sessions that cover such topics in analyses.

Participants will complete a survey approximately 2 weeks prior to departure, one survey during their first month abroad, one during their last month abroad, one during their first month back in the US, and a final follow up 3 months post-return to the US. The last survey completed abroad represents the final 30 days of the trip, which, for the majority of students in the study, will be the third month abroad. Length of program will be controlled for in analyses. Participants will receive a $20 Amazon gift card for each of these 15 to 20 min surveys that they complete. Email, text, and phone call reminders will assist with reducing attrition on surveys, which helped us retain 80% of participants in our pilot work and other RCTs [52, 76]. A diagram of participant flow through the intervention study is found in Fig. 1. Figure 2 contains a SPIRIT (Standard Protocol Items: Recommendations for Interventional Trials) flow diagram of the RCT schedule of enrollment, interventions, and assessments.

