##### Heavy drinking and alcohol-related consequences

Three prespecified drinking outcomes are total drinks per week, number of heavy drinking occasions, and number of alcohol-related consequences in the past 30 days. Drinking in the past 30 days will be assessed at all time points with the Daily Drinking Questionnaire (DDQ; [79]), which asks participants about their typical drinking on each day of a typical week in the past month. It will be used to generate the main drinking outcome of drinks per week but will also yield drinking variable we will look at descriptively (typical drinks consumed per occasion, drinking days per week). A single item will also assess frequency of heavy drinking (5+ drinks on one occasion for males; 4+ drinks on one occasion for females; known in some studies as “binge drinking”). Consequences from alcohol use in the past month will be assessed on all surveys with the 24-item Brief Young Adult Alcohol Consequences Questionnaire (B-YAACQ), a measure of negative consequences often used with the college population [80, 81]. The scale assesses alcohol-related consequences experienced in the past month (yes/no) with a sum score from 0 to 24.

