##### Risky sex

Risky sex (e.g., number of partners, use of condoms) in the past month will be assessed with the Sexual Risk Survey (SRS), a 23-item measure designed and validated with college student samples [82]. The SRS will be modified to assess past month behavior as opposed to past 6-month behavior so we can assess this outcome during equal time periods across surveys. The SRS allows for open-ended responses that are then recoded into ordinal categories for generating an overall score, as well as five composite scores of sexual risk taking with uncommitted partners, risky sex acts, impulsive sexual behaviors, intent to engage in risky sexual behavior, and risky anal sex acts [83]. A composite SRS score will be used in analyses as the risky sex outcome, with specific subscale scores examined descriptively.

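### Past-30-day recall at surveys taken at any point in the first month abroad or the first month back can count behaviour from the previous setting, and no survey day is fixed to prevent it

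*Protocol article*

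**What the plan says.** Procedures sets the follow-up timing: "one survey during their first month abroad, one during their last month abroad, one during their first month back in the US", then a final survey 3 months after return. It adds that the last survey abroad stands for the final 30 days of the trip. The two first-month surveys get no such anchor.

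The recall period is set with the outcomes. Under Heavy drinking and alcohol-related consequences, "Drinking in the past 30 days will be assessed at all time points with the Daily Drinking Questionnaire", an instrument that "asks participants about their typical drinking on each day of a typical week in the past month". The same section lists heavy drinking occasions among the past-30-day outcomes and says: "Consequences from alcohol use in the past month will be assessed on all surveys". Under Risky sex, the survey is changed from a 6-month to a past-month period "so we can assess this outcome during equal time periods across surveys".

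The Analytic plan makes the intervention effect at each of the four follow-ups the main analysis. Outcome measures predicts that effects seen abroad will persist after return. The Abstract, the Overview and the Analytic plan describe the first post-return survey as 1-month post-return; the Overview, for example, speaks of testing "on sustained effects once students return to campus at 1- month and 3- months post-return".

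**The concern.** Equal recall length does not ensure that the window lies in the setting it is named after. A student who answers one week after arrival reports mostly on life at home. A student who answers one week after return reports mostly on life abroad. Nothing in the article limits recall at these two surveys to time since arrival or since return. It does tie recall to the setting elsewhere: for the last abroad survey, and for sexual violence, which is asked about the whole trip and then about the time since return.

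Two of the four contrasts in the main analysis are exposed, for four of the five outcomes. At the first abroad survey, home days can pull the contrast toward zero. At the first post-return survey, days abroad can make an effect that stopped at return look sustained, and a sustained effect is one of the stated hypotheses.

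**Working it through.** **Inputs from the article.** Recall of 30 days (outcome sections). Predeparture survey about 14 days before departure (Procedures), with the intervention delivered immediately afterwards (Phase 2 RCT). 600 per arm and 80% retention in earlier work (Procedures), so 600 × 0.80 = 480 per arm if repeated.

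**The plan's own figure.** The total of 1200 cannot be reproduced, because the article gives no numerical effect size, alpha, power or standard deviation. It is not disputed here.

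**Step 1: share of the window in the previous setting.** For completion on day D, share = (30 − D)/30. Day 7: 23/30 = 77%. Day 15: 15/30 = 50%. Day 21: 9/30 = 30%. Day 28: 2/30 = 7%. Day 30: 0%. If completion were spread evenly over days 1 to 30, the mean would be 14.5/30 = 48%; that spread is an assumption.

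**Step 2: share before the intervention (first abroad survey).** Share = max(0, 30 − D − 14)/30. Day 7: 9/30 = 30%. Day 15: 1/30 = 3%. From day 16 on: 0%.

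**Step 3: illustration of the consequences.** Assumptions, none of them in the article:
- a standardised effect of 0.20 abroad and zero at home;
- scores that mix in proportion to days;
- 480 per arm, two-sided alpha 0.05, one time point, no clustering.

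Apparent first-abroad effect = 0.20 × D/30. Apparent post-return effect = 0.20 × (30 − D)/30. With z = effect/√(2/480), the rejection probability is Φ(z − 1.96) + Φ(−z − 1.96).

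| Completion day | First-abroad effect | Power | Post-return effect (true effect zero) | Chance of a significant result |
|---|---|---|---|---|
| 7 | 0.047 | 0.11 | 0.153 | 0.66 |
| 15 | 0.10 | 0.34 | 0.10 | 0.34 |
| 21 | 0.14 | 0.58 | 0.06 | 0.15 |
| 28 | 0.187 | 0.82 | 0.013 | 0.055 |
| 30 | 0.20 | 0.87 | 0 | 0.05 |

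Steps 1 and 2 are arithmetic on the stated timing and recall. Step 3 shows only how strongly the result depends on the survey day: by day 28 the problem has almost gone.

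**The case against.** The strongest reply is that the harm depends on a number the article does not give. Survey opening days are operational detail. The participant flow and schedule figures are not shown, and the full protocol may place both surveys at the end of the month. The last-month survey is described with the same wording and then equated with the final 30 days of the trip, which hints at end-of-month completion. The 1-month post-return label points the same way for the survey after return. All of this stands as a limit on size and certainty. It does not remove the point, because the timing and recall that the article does state permit a mismatch, and the two descriptions of the post-return survey differ.

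The instruments also weaken the linear illustration. The drinking questionnaire asks about a typical week, so a student three weeks into the stay may simply describe life abroad. Consequences are yes/no items over the month, and risky-sex answers are recoded to ordinal categories. Carry-over is plausible for these two, but none of the scores is a day-weighted average. The power figures also ignore the planned three-level model.

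A reader might infer more: that the trial will lose more than half its power at the first abroad survey, that a false sustained effect is to be expected, or that the randomised comparison is invalid. The documents support none of these. The first two need assumed completion days, an assumed effect and linear mixing. As to the third, both arms share the same schedule and recall, so the contrast remains valid for the window actually measured. What can be wrong is its label.

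**Conclusion.** The point holds as a mismatch between stated survey timing and stated recall at two of the four follow-ups, for drinks per week, heavy drinking, consequences and risky sex. Any survey answered before day 30 of the new setting includes 30 − D days of the old one. The first-abroad contrast can be diluted, and the first post-return contrast can take in behaviour abroad. The post-return part is the less certain, because it depends on which description of that survey applies.

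The size is unknown: negligible near day 30, and potentially large if many students answer in the first two weeks. The last-month-abroad survey is tied to the end of the trip, and a past-month window at 3 months lies wholly at home, so effects abroad and lasting effects can still be tested there. Sexual violence is not asked at the two surveys in question.

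**What to change.** - Open the first abroad survey at about day 28–30 after arrival and the first post-return survey at about day 28–30 after return, each with a short closing window.
- Record the completion day for every survey and run a sensitivity analysis limited to late completers. Read it with care, since completion day is determined after randomisation.
- Use one definition of the first post-return survey in the Abstract, Overview, Procedures and Analytic plan.

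This changes survey trigger dates and some wording, with no extra participants or surveys. The small downside is that the first abroad survey comes later in the month. In the shortest eligible programmes (8 weeks, 56 days), a day-30 window and the final 30 days would overlap by 60 − 56 = 4 days.

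Asking about time since arrival or since return, with elapsed days as exposure, is a secondary option only. It gives up the equal recall periods that the Risky sex section deliberately chose.
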